## Abstract

**Background:**

Insomnia is a highly prevalent condition, with heterogeneous clinical presentations and underlying mechanisms. Traditional assessment methods often fail to capture this complexity, thereby hindering the development of personalized treatments. This paper details a protocol for a study that employs a “deep phenotyping” approach to comprehensively characterize insomnia.

**Methods:**

This single-center prospective observational study recruited adults with insomnia and a parallel cohort of normal sleepers as the controls. Participants undergo a 4-week multimodal assessment. The assessment framework integrates four key data domains: (1) clinical assessment, involving self-reported data from a comprehensive battery of clinical and psychological questionnaires; (2) digital phenotyping, capturing real-world behavioral and physiological data through a wrist-worn wearable device and a smartphone application; (3) functional neuroimaging, using a baseline functional near-infrared spectroscopy (fNIRS) scan to measure prefrontal cortex activity; and (4) genomic and biomarker collection from blood samples for genomic and exploratory biomarker analyses. The study was conducted between March 2023 and October 2024, and all recruitment and data collection have been completed. The core analysis will employ advanced computational methods, including clustering and machine learning, to identify the distinct subtypes of insomnia.

**Discussion:**

By applying multivariate pattern analysis and machine learning techniques to this rich, integrated dataset, we aimed to identify distinct biopsychosocial phenotypes of insomnia. This deep phenotyping approach is expected to elucidate the heterogeneity of insomnia, paving the way for the development of targeted and personalized management strategies for individuals with sleep disorders.

**Clinical Trial Registration:**

Clinical Research Information Service KCT0009175; https://cris.nih.go.kr/cris/search/detailSearch.do?seq=26133

## Introduction

1

Insomnia is one of the most prevalent and impactful sleep disorders, affecting approximately 10% of adults chronically and an additional 30-35% experiencing occasional symptoms (1, 2). It is characterized by difficulty in initiating or maintaining sleep despite adequate opportunity and is frequently accompanied by daytime impairment (3–5).

The etiology of insomnia is complex and multifactorial. The development and persistence of insomnia are influenced by a combination of genetic factors (6, 7), psychological stress, maladaptive sleep habits, and cognitive factors (1, 8, 9). Circadian rhythm disruption (10), shift work (11), and comorbid medical (12) and psychiatric disorders (13) are also well-established risk factors.

Moreover, recent neuroimaging studies have suggested that individuals with insomnia may exhibit structural and functional alterations (14) in the brain regions associated with arousal, emotion regulation, and cognitive control, although the findings remain somewhat inconsistent (15). In parallel, emerging genetic research has highlighted the dysregulation of circadian clock genes that contribute to the pathophysiology of insomnia. These multilayered causes and the inherent heterogeneity of insomnia suggest that approaching it as a single symptom-based disorder is a fundamental limitation.

Conventional studies on insomnia in clinical practice have relied predominantly on patient-reported outcomes, including sleep questionnaires, sleep diaries, and clinical interviews. While polysomnography (PSG) and actigraphy offer more objective measures of sleep, their application is often limited to brief observation periods or specialized research settings. Consequently, traditional assessment approaches, which primarily focus on subjective symptoms or single-night metrics, often fail to capture the complex multidimensional complex nature of insomnia (16).

Ecological momentary assessment provides valuable real-time symptom data but remains limited by its reliance on subjective reports and narrow physiological measures, lacking insight into brain function and the biological underpinnings of insomnia (17, 18). Recent advances in digital phenotyping have enabled large-scale, real-time monitoring of sleep. However, such approaches are limited by the extreme complexity and heterogeneity of datasets and lack of subjective assessments (19, 20). In conclusion, fragmented approaches have a fundamental limitation in fully understanding the complex biopsychosocial characteristics of insomnia and identifying individual specificities.

Therefore, a multimodal assessment approach, commonly referred to as “deep phenotyping,” is essential to comprehensively unravel the complex and heterogeneous nature of insomnia. This approach seeks to integrate multiple levels of information, including the patients’ subjective experiences, objective sleep-wake patterns, neurophysiological activity, and genetic predispositions. Although recent studies have begun to explore such integrative frameworks, the field is still in its early stages. To overcome these limitations, this study outlines a research protocol designed to apply a deep phenotyping strategy to insomnia. Specifically, it combines data from standardized clinical questionnaires, continuous digital phenotyping using wearable devices and smartphone applications, functional neuroimaging via portable functional near-infrared spectroscopy (fNIRS), and genomic and biomarker analyses. Through this comprehensive, multimodal approach, we aim to identify the distinct phenotypic subtypes of insomnia. Ultimately, exploring the underlying biological and neurophysiological mechanisms of these subtypes may lead to a more refined understanding of the disorder and inform the development of personalized mechanism-based treatment strategies.

## Methods

2

### Study design

2.1

This study employed a single-center prospective observational design with two parallel cohorts, an insomnia group and a normal sleeper control group. The study was conducted at the Korea University Anam Hospital in Seoul, South Korea, and DataMaker Inc. in Daejeon, South Korea, between March 2023 and October 2024. The observational nature of the study allowed for the careful assessment and monitoring of participants’ sleep patterns, behaviors, and relevant physiological and biological parameters over a 4-week period. This duration was selected to capture a representative range of day-to-day fluctuations in sleep and daytime symptoms, while minimizing participant burden. A parallel-cohort design allows for the comparison of these measures between individuals with insomnia and those with normal sleep, enabling the identification of distinguishing features and potential subtypes of insomnia. The entire study consists of a baseline visit (week 0), a 4-week monitoring period (weeks 1-4), and an endpoint visit (week 4). An overview of this protocol is shown in **Figure 1**.

**Figure 1 f1:**
[figure not shown]
Protocol flow chart of the study fNIRS, functional near-infrared spectroscopy; ISI, Insomnia Severity Index; PSQI, Pittsburgh Sleep Quality Index; SHI, Sleep Health Index; SHPS, Sleep Hygiene and Practices Scale; BQ, Berlin Questionnaire; IRLS, International Restless Legs Syndrome Rating Scale; DBAS-16, Dysfunctional Beliefs and Attitudes about Sleep-16; MEQ, Morningness–Eveningness Questionnaire; BPS, Bedtime Procrastination Scale; FIRST, Ford Insomnia Response to Stress Test; STAI, State–Trait Anxiety Inventory; K-MDQ, Korean version of the Mood Disorder Questionnaire; BSQ, Body Sensations Questionnaire; KRQ-53, Korean Resilience Quotient-53; AUDIT, Alcohol Use Disorders Identification Test; SOS-Q, Smartphone Overuse Screening Questionnaire; SPAQ, Seasonal Pattern Assessment Questionnaire; BRIAN, Biological Rhythms Interview of Assessment in Neuropsychiatry; SWBS, Spiritual Well-Being Scale; ESS, Epworth Sleepiness Scale; PHQ-9, Patient Health Questionnaire-9; GAD-7, Generalized Anxiety Disorder-7; MFS, Multidimensional Fatigue Scale; IPAQ-SF, International Physical Activity Questionnaire–Short Form; WHOQOL-BREF, World Health Organization Quality of Life–BREF.

### Participants

2.2

This study will recruit two parallel cohorts, an insomnia group and a normal sleeper control group. The inclusion and exclusion criteria for each cohort will be carefully defined to ensure a homogeneous sample and minimize confounding factors.

Participants in the insomnia group will be adults aged 19–70 years who report experiencing subjective insomnia symptoms, such as difficulty initiating sleep, difficulty maintaining sleep, or early morning awakenings, for at least three nights per week over the preceding three months. A score of 15 or higher on the Insomnia Severity Index (ISI) will be required to ensure that participants experience at least a moderate level of insomnia (21).

The normal sleeper control group will also consist of adults aged 19–70 years. To be included, these individuals must report experiencing insomnia symptoms less than three times per month, have an ISI score of less than 8, and report an average sleep duration of six hours or more per night over the preceding three months. Controls have no history of chronic insomnia or any major psychiatric illness and will also be required to comply with all the study procedures.

All participants in both groups are required to be willing to comply with all the study procedures, including the use of wearable devices and smartphone applications.

To minimize the influence of confounding factors, individuals meeting any of the following criteria were excluded from participation in either group: evidence of other primary sleep disorders such as untreated sleep apnea, narcolepsy, or other sleep-related breathing disorders; a current diagnosis of a major psychiatric disorder, including major depression, bipolar disorder, or schizophrenia, or a severe substance use disorder; the presence of cognitive impairment or a neurological disorder that could preclude valid self-report or compliance; participation in shift work or maintenance of an irregular sleep schedule within the past three months; and lack of access to a compatible smartphone or unwillingness to use the study’s smartphone application. The current use of hypnotic medications or supplements that have a significant effect on sleep was also an exclusion criterion.

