#### Group comparison analyses

2.8.2

*Primary group comparisons*: Between-group differences (insomnia vs. controls) will be assessed using appropriate statistical tests based on the data distribution and measurement level. Independent samples t-tests (or Mann-Whitney U tests for non-normal distributions) will be used to compare continuous variables. Chi-square tests will evaluate categorical variables.

*Secondary analyses*: Subgroup comparisons will examine differences based on sleep disorder risk (e.g., RLS symptoms, sleep apnea risk) and demographic factors. Analysis of covariance (ANCOVA) will control for potential confounders, including age, sex, and comorbid conditions.

*Multiple comparisons*: Given the large number of variables, false discovery rate (FDR) correction using the Benjamini-Hochberg procedure will be applied to control for multiple testing. Both uncorrected and FDR-corrected p-values will be reported to balance the discovery and rigor.

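### Controls are barred for any history of major psychiatric illness but insomnia participants only for a current diagnosis, so the group contrast carries a built-in difference that the plan neither removes nor discloses

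*Protocol article*

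**What the plan says.** Section 2.2 (Participants) of the protocol article states that the criteria "will be carefully defined to ensure a homogeneous sample and minimize confounding factors". It then gives:

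- **Insomnia group.** Age 19–70, symptom frequency and duration, and severity: "A score of 15 or higher on the Insomnia Severity Index (ISI) will be required". No criterion concerns psychiatric history.
- **Control group.** "Controls have no history of chronic insomnia or any major psychiatric illness and will also be required to comply with all the study procedures". No time limit is attached.
- **Both groups.** The shared list opens with "individuals meeting any of the following criteria were excluded from participation in either group" and its psychiatric item is "a current diagnosis of a major psychiatric disorder, including major depression, bipolar disorder, or schizophrenia, or a severe substance use disorder".

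Section 2.1 describes the contrast as one of sleep status: "A parallel-cohort design allows for the comparison of these measures between individuals with insomnia and those with normal sleep". Section 2.8 makes the difference between the insomnia and control groups the first of three primary objectives.

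Under section 2.8.2 the primary comparisons are t-tests, Mann-Whitney tests or chi-square tests, without covariates. Adjustment appears among the secondary analyses: "Analysis of covariance (ANCOVA) will control for potential confounders, including age, sex, and comorbid conditions". The limitations in the Discussion mention the exclusion of major psychiatric disorders only as a limit on applicability.

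**The concern.** The shared exclusion is the only psychiatric rule that binds the insomnia group, and it looks at the present. The control rule also looks back. The two groups are thus selected differently on a second variable, past major psychiatric illness: it is absent from the control group by rule and allowed in the insomnia group where no current diagnosis remains.

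Several outcomes compared between groups are plausibly related to that variable, most clearly PHQ-9, GAD-7, STAI trait anxiety, BSQ and KRQ-53, as well as the K-MDQ, which asks about lifetime symptoms. Part of a difference on these measures, or part of the accuracy of an insomnia-versus-control classifier, could come from controls selected for having no such history. The FDR procedure limits chance findings and cross-validation limits overfitting. Neither removes a difference created by how the groups were chosen.

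**Working it through.** **1. The rules side by side (section 2.2)**

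| | Current diagnosis | Past illness, no current diagnosis |
|---|---|---|
| Insomnia | excluded | eligible |
| Control | excluded | excluded |

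The asymmetry lies in the last column.

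**2. The plan's own figure.** Section 2.9 gives about 80% power at d ≈ 0.36 with at least 240 insomnia participants and 80 controls, α = 0.05. Two-sided detectable d at 80% power, normal approximation:

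(1.960 + 0.842) × √(1/240 + 1/80) = 2.802 × 0.1291 = 0.362.

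Power at d = 0.36 is 79.6% (79.4% by noncentral t). The stated figure reproduces. With the enrolled 249 and 89, the detectable d is 2.802 × 0.1235 = 0.346.

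**3. Size of the built-in shift.** Let p be the share of insomnia participants with past illness and g its effect on an outcome in SD. The document gives neither; the ranges p = 10–40% and g = 0.2–0.8 are assumptions. With no true insomnia effect:

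- shift = p × g
- SE = √([1 + p(1 − p)g²]/249 + 1/89)
- rejection rate at two-sided 0.05, uncorrected = 1 − Φ(1.96 − shift/SE) + Φ(−1.96 − shift/SE)

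For p = 20%, g = 0.5: shift = 0.10; SE = √(1.04/249 + 1/89) = 0.124; ratio 0.81; rejection 12.7%.

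| p | g (SD) | Shift (SD) | Share of 0.36 | Rejection rate |
|---|---|---|---|---|
| 10% | 0.2 | 0.02 | 6% | 5.3% |
| 10% | 0.5 | 0.05 | 14% | 6.9% |
| 30% | 0.2 | 0.06 | 17% | 7.7% |
| 20% | 0.5 | 0.10 | 28% | 12.7% |
| 30% | 0.5 | 0.15 | 42% | 22.6% |
| 40% | 0.8 | 0.32 | 89% | 71.9% |

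**4. Can adjustment repair it?** Past illness is zero in every control by rule. A covariate for it would be estimated from the insomnia group alone, with no overlap between groups, so the corrected contrast would rest on the model. Restricting the insomnia group avoids this.

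**5. What restriction costs.** Detectable d at 80% power (noncentral t), against 89 controls:

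| Insomnia participants | Detectable d |
|---|---|
| 249 (all enrolled) | 0.347 |
| 199 (20% dropped) | 0.358 |
| 174 (30% dropped) | 0.366 |

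Section 2.9 reports 130 of the 249 as mild on the ISI, whereas section 2.2 requires 15 or more. If only the other 119 (101 + 18) counted as eligible, the values would be 0.394 before restriction, and 0.415 (95 vs 89) or 0.430 (83 vs 89) after losing 20% or 30%.

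**The case against.** **Carefully selected controls are a legitimate choice.** Objective 1 is descriptive, the Discussion disclaims causal inference, and section 2.4.2 notes that sleep and mental health influence each other in both directions. If past psychiatric illness is partly a consequence of insomnia, removing those participants removes part of the phenotype. This stands. It is the reason to keep the full comparison and to use restriction as a sensitivity analysis. It does not excuse leaving the comparator undescribed.

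**The size is unknown.** This also stands. Both inputs are assumed, and at the low end the shift is negligible. The rejection rates are for uncorrected tests under a true null, whereas FDR correction is planned.

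**History may not be on file for the insomnia group.** Table 1 lists no psychiatric-history instrument apart from the K-MDQ, a screen for manic and hypomanic symptoms. The full protocol may collect more. The restricted analysis is therefore conditional.

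Four stronger readings are tempting but not supported:

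- *That psychiatric history is unrestricted in the insomnia group, or that past bipolar disorder is eligible.* The shared rule refers to a diagnosis, not an episode, and someone with past bipolar episodes may still carry the diagnosis. The clear gap is remitted illness that no longer carries one.
- *That comorbid conditions in the ANCOVA means present conditions only.* The article does not define the term, and the covariate list is open.
- *That every outcome is biased away from the null.* This needs past illness to shift the outcome in the same direction as insomnia. That is plausible for mood, anxiety and resilience. Nothing in the document supports it for fNIRS, gene expression or the polygenic score, and the Introduction calls the neuroimaging findings somewhat inconsistent.
- *That the whole study is affected.* The abstract describes subtype identification as the core analysis, and clustering within the insomnia group does not use the controls.

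**Conclusion.** The point holds in limited form. The criteria create a difference in past psychiatric illness between the groups, the unadjusted primary comparisons leave it in place, and the limitations do not mention it. As the plan stands, objective 1 can credit to insomnia a difference that comes partly from controls with no psychiatric history.

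The existence of the asymmetry follows from the text alone. Its size does not: under the assumed ranges the shift runs from 0.02 to 0.32 SD, or 6% to 89% of the planned detectable effect, with 0.10 SD (28%) at p = 20% and g = 0.5. Equal rules would remove only the part imposed by the criteria; any natural difference in past illness between people with insomnia and normal sleepers would remain. This should be addressed before the group contrasts are interpreted, but it does not invalidate the study.

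**What to change.** Recruitment is complete, so the change is to analysis and reporting.

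1. **Section 2.8.2.** Keep the full insomnia-versus-control comparison. If lifetime psychiatric history was recorded for insomnia participants, pre-specify a sensitivity comparison, and a matching classifier run under section 2.8.5, restricted to insomnia participants with no history of major psychiatric illness. Report it beside the full result, with the number excluded.
2. **Objective 1 and its conclusions.** Whether or not history was recorded, describe the comparator as normal sleepers with no history of major psychiatric illness.
3. **Limitations.** State that the psychiatric criterion differed between the groups.
4. **Interpretation.** Do not attribute a group difference to insomnia alone unless it persists in the restricted comparison. If that comparison cannot be run, leave the attribution open.

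The cost is some wording and one additional run where the data exist. The restricted run loses some precision: detectable d moves from about 0.35 to 0.36–0.37 if 20–30% of the 249 drop out, and is larger if fewer insomnia participants are eligible or have data for a given modality. The subtype analyses keep all insomnia participants.

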### Clinical assessments

2.4

A comprehensive battery of validated clinical assessment instruments will be employed to characterize participants across multiple domains relevant to sleep, psychological functioning, and general health. These instruments are selected based on their psychometric properties, clinical relevance, and established uses in sleep research. Basic demographic information, including age, sex, work patterns, lifestyle factors, height, and weight are collected at the baseline. A detailed summary of all instruments, including the administration schedule and scoring, is provided in **Table 1**.

**Table 1 T1:** Clinical assessment instruments.

Domain	Instrument (Abbreviation)	Administration Schedule	Scoring Range & Interpretation
Sleep-Related Assessments	Insomnia Severity Index (ISI)	Baseline, Weekly (via app), Week 4	7 items, 0–4 each (Total: 0–28). 0-7: No significant insomnia; 8-14: Mild; 15-21: Moderate; 22-28: Severe insomnia.
	Pittsburgh Sleep Quality Index (PSQI)	Baseline	19 items across 7 components (Total: 0–21). Global score >5 indicates poor sleep quality. Higher scores = worse sleep.
	Epworth Sleepiness Scale (ESS)	Baseline, Week 4	8 items, 0–3 each (Total: 0–24). >10 indicates excessive daytime sleepiness. Higher scores = greater sleepiness.
	Sleep Health Index (SHI)	Baseline	14 items across 3 domains (Total: 0–100). Higher scores indicate better sleep health. Assesses sleep quality, duration, and disordered sleep.
	Sleep Hygiene and Practices Scale (SHPS)	Baseline	30 items, 1–6 Likert scale (Total: 30–180). Higher scores indicate poorer sleep hygiene practices.
	Berlin Questionnaire (BQ)	Baseline	10 items across 3 categories. High risk if ≥2 categories positive. Screens for obstructive sleep apnea risk.
	International Restless Legs Syndrome Rating Scale (IRLS)	Baseline	10 items, 0–4 each (Total: 0–40). 0-10: Mild; 11-20: Moderate; 21-30: Severe; 31-40: Very severe RLS.
	Dysfunctional Beliefs and Attitudes about Sleep-16 (DBAS-16)	Baseline	16 items, 0–10 Likert scale. Mean score calculated (Range: 0–10). Higher scores = more dysfunctional sleep beliefs.
	Morningness-Eveningness Questionnaire (MEQ)	Baseline	19 items (Total: 16–86). Higher scores = morning preference; lower scores = evening preference. Determines chronotype.
	Bedtime Procrastination Scale (BPS)	Baseline	9 items, 1–5 Likert scale (Total: 9–45). Higher scores indicate greater bedtime procrastination tendency.
	Ford Insomnia Response to Stress Test (FIRST)	Baseline	9 items, 1–4 Likert scale (Total: 9–36). Higher scores = greater vulnerability to stress-induced insomnia.
Psychological and Mental Health Assessments	State-Trait Anxiety Inventory (STAI)	Baseline	40 items: 20 state + 20 trait items, 1–4 each (Range: 20–80 per subscale). Higher scores = greater anxiety.
	Patient Health Questionnaire-9 (PHQ-9)	Baseline, Week 4	9 items, 0–3 each (Total: 0–27). 5-9: Mild; 10-14: Moderate; 15-19: Moderately severe; 20-27: Severe depression.
	Generalized Anxiety Disorder-7 (GAD-7)	Baseline, Week 4	7 items, 0–3 each (Total: 0–21). 5-9: Mild; 10-14: Moderate; ≥15: Severe anxiety.
	Korean version of Mood Disorder Questionnaire (K-MDQ)	Baseline	13 yes/no items. Positive screen if ≥7 yes responses. Screens for bipolar spectrum disorders.
	Body Sensations Questionnaire (BSQ)	Baseline	17 items, 1–5 Likert scale. Mean score calculated. Higher scores = greater fear of autonomic sensations.
	Korean Resilience Quotient-53 (KRQ-53)	Baseline	53 items, 1–5 Likert scale across 3 domains. Higher scores indicate greater psychological resilience.
General Health and Lifestyle Assessments	Multidimensional Fatigue Scale (MFS)	Baseline, Week 4	18 items, 1–5 Likert scale (Total: 18–90). Assesses general, sleep/rest, and cognitive fatigue. Higher scores = greater fatigue.
	Alcohol Use Disorders Identification Test (AUDIT)	Baseline	10 items, 0–4 each (Total: 0–40). ≥8 indicates hazardous drinking; ≥20 suggests possible dependence.
	Smartphone Overuse Screening Questionnaire (SOS-Q)	Baseline	28 items, 1–4 point scale (Total: 28–112). Score ≥49 indicates high smartphone addiction risk.
	Seasonal Pattern Assessment Questionnaire (SPAQ)	Baseline	6 behavioral items, 0–4 each + severity rating. Global Seasonality Score ≥11 with marked problems suggests SAD.
	Biological Rhythms Interview of Assessment in Neuropsychiatry (BRIAN)	Baseline	18 items, 1–4 scale + 3 chronotype items (Total: 18–72). Higher scores indicate greater circadian rhythm disturbance.
	Spiritual Well-Being Scale (SWBS)	Baseline	20 items, 1–6 Likert scale (Total: 20–120). Comprises Religious (RWB) and Existential (EWB) subscales. Higher scores = better well-being.
	International Physical Activity Questionnaire-Short Form (IPAQ-SF)	Baseline, Week 4	7 items assessing walking, moderate, and vigorous activity. Results expressed as MET-minutes/week. Categorizes activity level.
	WHO Quality of Life-BREF (WHOQOL-BREF)	Baseline, Week 4	26 items across 4 domains, 1–5 scale. Domain scores transformed to 0–100 scale. Higher scores = better quality of life.

ISI, Insomnia Severity Index; PSQI, Pittsburgh Sleep Quality Index; ESS, Epworth Sleepiness Scale; SHI, Sleep Health Index; SHPS, Sleep Hygiene and Practices Scale; BQ, Berlin Questionnaire; IRLS, International Restless Legs Syndrome Rating Scale; DBAS-16, Dysfunctional Beliefs and Attitudes about Sleep-16; MEQ, Morningness-Eveningness Questionnaire; BPS, Bedtime Procrastination Scale; FIRST, Ford Insomnia Response to Stress Test; STAI, State-Trait Anxiety Inventory; PHQ-9, Patient Health Questionnaire-9; GAD-7, Generalized Anxiety Disorder-7; K-MDQ, Korean version of Mood Disorder Questionnaire; BSQ, Body Sensations Questionnaire; KRQ-53, Korean Resilience Quotient-53; MFS, Multidimensional Fatigue Scale; AUDIT-K, Alcohol Use Disorders Identification Test-Korea; AUDIT-C, Alcohol Use Disorders Identification Test-Consumption; SOS-Q, Smartphone Overuse Screening Questionnaire; SPAQ, Seasonal Pattern Assessment Questionnaire; K-BRIAN, Korean version of Biological Rhythms Interview of Assessment in Neuropsychiatry; SWBS, Spiritual Well-Being Scale; IPAQ-SF, International Physical Activity Questionnaire-Short Form; WHOQOL-BREF, World Health Organization Quality of Life-BREF; MET, Metabolic Equivalent of Task; SAD, Seasonal Affective Disorder; RWB, Religious Well-Being; EWB, Existential Well-Being.

